### **9.4.2 AEs & Unrelated SAEs**

Anticipated AEs or unrelated SAEs will be handled in a less urgent manner but will be reported to the DSMC, IRB, and funding agency (PCORI). All individual AE and Safety reports will be maintained by the investigator and a summary (not individual reports) of all adverse events that have occurred within the last approval period that are associated with the study, whether related or non-related, will be submitted to the IRB at the time of continuing review. These reports will also be submitted to the DSMC and the funding agency (PCORI) during the yearly DSMC meetings.

Adverse events may include a participant's death as a result of a longtime illness (non-related), a breach in confidentiality, or any complaint of a participant unless the risk involved is serious (in which case, the event is reported as an unanticipated problem involving risk to participants or others or as a serious adverse event at the time of occurrence).

### **9.4.3 Unanticipated Problems**

Incidents or events that meet the OHRP criteria for unanticipated problems will be recorded in an event report form. The following information will be included when reporting an adverse event, or any other incident, experience, or outcome as an unanticipated problem to the IRB:

- appropriate identifying information for the research protocol, such as the title, investigator's name, and the IRB project number;
- a detailed description of the adverse event, incident, experience, or outcome;
- an explanation of the basis for determining that the adverse event, incident, experience, or outcome represents an unanticipated problem;
- a description of any changes to the protocol or other corrective actions that have been taken or are proposed in response to the unanticipated problem.

To satisfy the requirement for prompt reporting, unanticipated problems will be reported using the following timeline:

- Unanticipated problems that are serious adverse events will be reported to the IRB and PCORI within 7 calendar days of the investigator becoming aware of the event.
- Any other unanticipated problem will be reported to the IRB, the funding agency (PCORI), and the DSMC in a less urgent manner during annual continuing review and DSMC meetings.

## **9.5 Halting Rules**

While the comparison of treatment arms is novel, the actual therapy in each treatment arms is not. All procedures are standardized, and potential adverse events are well understood. The surgery is an outpatient procedure with very low risk. Nonetheless, a continuous monitoring rule for monitoring SAE has been developed for the DSMC to ensure the SAE rate does not exceed 10%.

## **10 STUDY OVERSIGHT**

The study oversight committees will be active for the primary study/trial and dissolve at the end of the primary study. They will not be active for the sub-study.

### **10.1 Data and Safety Monitoring Committee (DSMC)**

In addition to the PI's responsibility for oversight, study oversight will be under the direction of a Data and Safety Monitoring Committee (DSMC) composed of members with expertise in orthopedic surgery, physical therapy, musculoskeletal research, and biostatistics as well a lay community member. The DSMC will operate under the rules of a charter that will be approved at the organizational meeting of the DSMC. The DSMC for this study is convened for the primary study (and not the sub-study).

The DSMC will meet annually, or more frequently at their discretion, to assess safety and efficacy data, study progress, and data integrity for the study. If safety concerns arise, more frequent meetings may be held. At the end of each meeting the DSMC will make a formal recommendation regarding the continuation of the study.

### **10.2 Scientific Advisory Board**

A Scientific Advisory Board of international experts from various disciplines relevant to this trial will meet once per year along with investigators from all sites to review progress, potential trial challenges, discuss methodology issues, and ensure that the study's work reflects evolving clinical science.

### **10.3 Study Steering Committee**

The Steering Committee will be comprised of the study principal investigator (who will serve as Chair), individual site principal investigators, and other members selected for their content expertise as advisors to the Steering Committee. The Steering Committee will meet monthly or every other month to closely monitor trial operations, ensure adequate study accrual, protocol compliance, timely data entry, ensure implementation of the recommendations of the DSMC, and general study integrity.

### **10.4 Stakeholder Advisory Board**

A Stakeholder Advisory Board comprised of a diverse group of individuals with an interest in rotator cuff tears, including patients, their caregivers, and insurance and medical industry representatives, will advise in the development of study materials and the conduct of the study as it relates to study participants. The Stakeholder Advisory Board will meet approximately every other month to review the progress of the trial.

## **11 CLINICAL SITE MONITORING**

Internal clinical site monitoring will be conducted to ensure that the rights of human subjects are protected, that the study is implemented in accordance with the protocol and/or other operating procedures, and that the quality and integrity of study data and data collection methods are maintained. Monitoring for this study will be performed by the study PI and by the executive study coordinator, who will review data and documentation regularly and visit sites as needed. A monitoring report generated from data within the study REDCap databases will be created and used to track and monitor data completion and study activities. These monitoring activities will be performed for the primary study.

### **11.1 Screening/Enrollment Monitoring Reports**

The screening and enrollment data for each site will be reviewed monthly by the executive study coordinator and study PI to ensure that potentially eligible study participants are being screened, approached and consented as appropriate and study-related documents and images are submitted in accordance with the study protocol and Manual of Operating Procedures (MOOP). During the main study, study data analysts will prepare a monthly report of requested information drawn from study records in REDCap.

### **11.2 Site Monitoring Calls**

All sites will participate in regular site calls with the executive study coordinator to review data from Screening, Enrollment & Data reports. Call participants, notes regarding what was discussed, and any actions to be taken will be recorded and reviewed periodically by the study PI. Issues of immediate concern will be brought to the attention of the study PI as they are identified.

### **11.3 Site Visits**

If issues or questions of concern pertaining to site operations arise during the course of the study, the study PI &/or executive study coordinator may visit the site in person to observe how site procedures are being implemented and determine appropriate remedies, if needed.

Sites may also be visited within the first year of recruitment to ensure everything is operating correctly and to address any operational questions or challenges, as deemed appropriate by the study PI.

## 12 STATISTICAL CONSIDERATIONS

### 12.1 Study Hypotheses

**Aim 1:** To compare pain and function in patients undergoing operative versus non-operative treatment of atraumatic rotator cuff tears at 12 months of follow-up.

**Hypothesis 1:** Patients undergoing operative treatment will have significantly greater improvement in pain reduction and function (measured by SPADI) as compared with those treated non-operatively at 12 months of follow-up.

**Aim 2:** To assess effects of rotator cuff tear size and age on comparative outcomes (measured by SPADI) in operative versus non-operative treatments for atraumatic rotator cuff tears.

**Hypothesis 2a:** Surgery will be more effective than non-operative treatment in cuff tears of increasing size.

**Hypothesis 2b:** Surgery will be more effective than non-operative treatment of rotator cuff tears with decreasing age.

### 12.2 Final Analysis Plan

**Overview:** We are planning a trial where patients will be randomly assigned in equal proportion to operative or non-operative care.

**Primary Endpoint:** The primary outcome measure is SPADI, and the primary endpoint is the change in SPADI at 12 months relative to baseline. SPADI is measured on a scale of zero to 100, with lower scores for better outcomes. SPADI is a reliable and valid measure of shoulder function.

**Secondary Endpoint(s):** ASES-SF, cross-sectionally and longitudinally over time.

**Analysis Population:** We define the intent-to-treat (ITT) population as the group of patients randomized to a treatment arm regardless of any other consideration.

#### 12.2.1 Primary Analysis

The primary analysis will be conducted on the intent-to-treat (ITT) population as defined above. The distribution of 12-month change in SPADI, stratified by treatment

arm, will be summarized graphically with histograms, boxplots, and plots of CDFs as appropriate. Our primary analysis for testing the 3 specific hypothesis in section 12.1 will be conducted in the context of a mixed model. That model is,

$$y_{ij} = \beta_0 + \beta_1 I_{\{TRT_i=op\}} + \beta_2 t_{ij} + \beta_3 I_{\{TRT_i=op\}} t_{ij} + \beta_4 (tearsize_i) + \beta_5 (age_i) + \beta_6 (I_{\{TRT_i=op\}} * tearsize_i) + \beta_7 (I_{\{TRT_i=op\}} * age_i) + u_i + e_{ij}$$

where  $y_{ij}$  represents the change in SPADI from baseline for participant  $i = 1, \dots, n$  at time  $j = 3, 6, 12$  months who was assigned to management arm  $TRT_i$  ( $I_{\{TRT_i=op\}} = 1$  if participant  $i$  is on the Operative arm and 0 otherwise).  $\beta_0$  is the intercept,  $\beta_3$  is differential change in SPADI score over time due to treatment (i.e., the treatment effect over time; assumed linear here but it will be modeled flexibly as needed),  $\beta_4$  and  $\beta_5$  are the effects of tear size and age at the beginning of treatment, and  $\beta_6$  and  $\beta_7$  are the tear size and age interactions with treatment that potentially will help identify those patients most likely benefit from therapy. The first 8 terms represent fixed effects. The last 2 terms represent a patient specific random intercept to model the effects of study site and residual error, respectively. The estimate of interest from this longitudinal model is the predicted differential in 12-month SPADI change ( $\Delta\Delta SPADI_{12}$ ; 1st  $\Delta$  is for treatment change, 2nd  $\Delta$  is for 12-month change), which is typically estimated as a contrast or difference in predicted 12-month SPADI change.

A directly parallel analysis will also be conducted, where  $y_{ij}$  represents SPADI for participant  $i = 1, \dots, n$  at time  $j = 3, 6, 12$  months with baseline SPADI as a covariate. In the first model, analyses might lead to a statement such as “Pain and function improved over 12 months in the operative (non-operative) care group 11 points more on average compared to patients treated with non-operative (operative) therapy. In the second model, analyses may lead to a statement such as, “At 12 months, mean SPADI scores were 11 points lower in the non-operative (or operative) group.”

A restricted cubic spline may be fit for continuous covariates to allow for nonlinearity. Further, we will examine different parameterizations of “time” to appropriately capture longitudinal trends (e.g., we might use a time-squared term or let time be categorical). To account for site-to-site variation, the model will include either a fixed effect or random effect for sites (not shown here). The choice between a fixed and random effect often generates debate. While our general preference is to use a random effect, and that is our stated plan here, we realize that with multiple sites the resulting random effect estimates could be unstable due to imbalance in the number

of recruitments, especially if there are pronounced aggregate covariate dissimilarities across sites. In such a case, we will use a fixed effect for site. For completeness, we will report the unadjusted estimates for  $\Delta\Delta\text{SPADI}_{12}$  that results when  $Z_i$  is removed from the model. Note that in a randomized study the purpose of covariate adjustment in a regression model is to obtain unbiased estimates of effects accounting for the enormous variation typical of longitudinal studies.

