## 2.3 Hypotheses

Our hypotheses for the primary analysis at year one follow-up are:

**Hypothesis 1:** Patients undergoing operative treatment will have significantly greater improvement in pain reduction and function (measured by baseline to 12 month change in SPADI) as compared with those treated non-operatively at 12 months of follow-up.

**Hypothesis 2a:** Operative treatment will be more effective than non-operative treatment in cuff tears of increasing size.

**Hypothesis 2b:** Operative treatment will be more effective than non-operative treatment of rotator cuff tears with decreasing age.

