## 12.3 Sample Size Considerations

### 12.3.1 Primary Aim

A longitudinal mixed model will be used to compare the 12-month change in SPADI between treatment arms. The operating characteristics of this plan depend on the marginal distribution of  $\square\text{SPADI}_{12}$ , the assumed true distributional shift, and observed covariate patterns. Figure 3 displays the marginal distribution of  $\square\text{SPADI}_{12}$  for patients by treatment group. These distributions were derived from preliminary data taken from an ongoing prospective, non-randomized cohort of patient with degenerative rotator cuff tears receiving either non-operative or operative intervention. The mean  $\square\text{SPADI}_{12}$  was -16.7 (SD=24.2; n=72) overall. Current estimates for non-operative therapy are -12.3 (SD=21.55; n=45) and -40.6 (SD=19.14; n=27).

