### 12.3.3 Sample Size Projections

A sample size of 700 participants (350 per treatment group) provides excellent power even with significant levels of dropout/lost-to-follow-up rate (a two-sided Type I Error of 0.05 was used). Figure 4 illustrates the power for three different tests of  $\Delta\Delta\text{SPADI}_{12}$ . The black line shows the power for a simple t-test of 12-month SPADI change scores between treatment groups. The red line shows the power for a least squared means Wald test of the 12-month SPADI change scores between groups, but adjusted for baseline

covariates (mixed model with complete case analysis). The blue line shows the power for the same test from the mixed model, but when multiple imputation is used to properly account for the large number of missing observations in the preliminary data (RVI is 0.53). Here, RVI is the average relative increase (averaged over all coefficients) in variance estimates due to missing values. The largest fraction of missing information (FMI) is 0.412. Interestingly, rather than gaining efficiency, the MI mixed

model appears less efficient. Because the MI model properly accounts for variability in the presence of missingness, we can use this model to anticipate a loss of power due to missing data. These curves are based on the estimated standard deviation from the preliminary data: (black) t-test on available data, (red) mixed model on complete case data, (blue) multiply imputed mixed model. The dotted line shows the power to detect the same minimally clinically meaningful change in binary subgroups across treatment groups (e.g., gender by treatment interactions). The standard deviations for these curves were similarly derived from preliminary data. This approach allows us to carefully leverage preliminary data to anticipate cluster correlation, covariate effects, missing data patterns, and longitudinal correlation patterns. These projections are conservative.

To be clear, power for the adjusted mixed model reaches 90% at 60 patients per group. With the increased variance from imputation, power reaches 90% with 82

[figure not shown]

**Figure 4.** Power curves for primary treatment comparison (solid lines) and interactions (dashed lines) from covariate adjusted

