patients in each treatment group. For the unadjusted t-test, 90% power is achieved with 91 patients per treatment group. For the subgroup/patient heterogeneity analyses, 80% power to detect a 2-way interaction as small as the MCID is achieved with 122 patients per group (total n=488) for the imputed data set. Consequently, we expect to have excellent power to detect heterogeneous treatment effects, even in the presence of significant missing data (FMI was 0.41). Lastly, we note that in our preliminary data, the intraclass correlation coefficient (ICC) for institution was 0.04 (essentially zero) and largely inconsequential given the longitudinal correlation in SPADI measurements. If necessary, our approach permits the sequestering of site-to-site variability from residual error, increasing power for detecting fixed effects in the data.

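### Two sections assign three hypotheses to the primary analysis while others treat only the overall 12-month contrast as primary; the protocol should name one

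*Protocol*

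**What the plan says.** Two passages put three hypotheses into the primary analysis. Section 2.3 introduces H1, H2a and H2b with "Our hypotheses for the primary analysis at year one follow-up are". Section 12.2.1 repeats the assignment: "Our primary analysis for testing the 3 specific hypothesis in section 12.1 will be conducted in the context of a mixed model". The heterogeneity analysis of age and tear size sits inside 12.2.1 as part of the same model. Section 12.2.2 (Secondary Analyses) deals with ASES-SF and other outcomes and gives H2a and H2b no secondary status. Section 12.1 lists Aims 1 and 2 without ranking them.

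Other passages single out the overall treatment contrast:

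- The précis describes the primary study and analysis as the one-year comparison of pain and function.
- Section 12.2 names one endpoint: "the primary endpoint is the change in SPADI at 12 months relative to baseline".
- Section 12.2.1 itself gives one target: "The estimate of interest from this longitudinal model is the predicted differential in 12-month SPADI change".
- Section 12.3.1, headed Primary Aim, covers only the between-arm test: "A longitudinal mixed model will be used to compare the 12-month change in SPADI between treatment arms".
- Section 12.3.2 states a null hypothesis for Aim 1 only.
- The Figure 4 caption separates the two kinds of test: "Power curves for primary treatment comparison (solid lines) and interactions (dashed lines) from covariate adjusted".

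On error control, the only statement is in the sample-size section: "a two-sided Type I Error of 0.05 was used". The same section gives sample sizes for the overall test and for a two-way interaction, and concludes that "we expect to have excellent power to detect heterogeneous treatment effects".

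**The concern.** A reader of 2.3 and 12.2.1 would take all three hypotheses as primary. A reader of 12.3.1 and Figure 4 would take one. H2a and H2b are worded as directional claims that surgery does better with larger tears and at younger ages, so the difference affects what may be claimed.

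Two situations show what is at stake. If H1 is not significant but one interaction reaches p<0.05, sections 2.3 and 12.2.1 could be cited to report a confirmed primary hypothesis, and the other sections could be cited against it. If H1 is significant, which the preliminary arm means (-12.3 and -40.6 in 12.3.1) suggest the planners expected, a false claim could still arise about which patients benefit, and two unadjusted tests bear on that. The status of the interaction claims should be settled before results are known.

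**Working it through.** **Inputs from the protocol.** Effect 10 SPADI points (12.3.2). Preliminary SDs 21.55 (n=45) and 19.14 (n=27) (12.3.1). Two-sided 0.05, and 350 per arm (12.3.3). For 90% power, 91 per group with the unadjusted t-test and 82 per group with the imputed mixed model. For 80% power on an interaction, 122 per cell, 488 in total (12.3.3). The protocol gives no correlations between test statistics and no numerical dropout rate, so those used below are assumptions.

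**Step 1: which level was used for the overall test.** Pooled SD = sqrt[(44 × 21.55² + 26 × 19.14²)/70] = 20.69. Normal formula: n = 2 × [20.69 × (1.960 + 1.282)/10]² ≈ 90 per group. Exact t-test power at 91 per group is 90.03%. The stated 91 is reproduced at unadjusted two-sided 0.05. A one-sided 0.05 test gives 74, and a two-sided 0.05/3 gives 116; neither matches.

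**Step 2: which level was used for the interaction.** The SD implied by 82 per group is 10 × sqrt(82/2)/(1.960 + 1.282) = 19.75. For a difference of differences over four equal cells, n per cell = 4 × [19.75 × (1.960 + 0.842)/10]² = 122.5; power at 122 is 79.8%. The stated 122 is reproduced at unadjusted two-sided 0.05. One-sided gives 96.5 per cell and 0.05/3 gives 163.4.

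Both kinds of test were therefore planned at the full 0.05.

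**Step 3: chance of at least one false claim under each reading.**

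| Reading | Rate |
|---|---|
| H1 alone is primary | 5% |
| All three are claims, all nulls true, independent: 1 − 0.95³ | 14.3% |
| Same, all three equally correlated 0.2 / 0.5 / 0.8 (assumed) | 13.9% / 12.5% / 9.8% |
| Same, only the two interactions correlated 0.2 / 0.5 / 0.8 (assumed) | 14.1% / 13.6% / 12.4% |
| H1 truly positive, both interactions null, independent: 1 − 0.95² | 9.75% |
| All three are claims, all nulls true, independent, hypothesised direction only: 1 − 0.975³ | 7.3% |

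The correlated rows are simulations (3 million draws).

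**Step 4: price of Holm on the interaction pair.** Power for a 10-point binary interaction, equal cells, SD 19.75, is Φ(10/[19.75 × sqrt(4/n per cell)] − z), with z = 1.960 at 0.05 and 2.241 at 0.025 (the first Holm step).

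| Analysed | Per cell | At 0.05 | At 0.025 |
|---|---|---|---|
| 700 | 175 | 91.7% | 86.6% |
| 560 (20% loss, assumed) | 140 | 85.0% | 77.4% |
| 488 | 122 | 79.8% | 71.0% |

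**Step 5: what Holm on the pair does not do.** With H1 at 0.05 and an ungated Holm pair, all nulls true and independent, the chance of any false rejection is 1 − 0.95 × 0.975² = 9.7%. Joint control of all three at 5% needs the pair to be tested only if H1 is rejected.

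**The case against.** The strongest reply is that the protocol does single out H1. It has one endpoint, one estimate of interest, one Primary Aim, one stated null, a separate heading for heterogeneity, and a figure caption that reserves the word primary for the treatment comparison. Section 12.2.1 also speaks of the interactions as potentially helping to identify patients who benefit, which is not confirmatory language. On this view the phrases in 2.3 and 12.2.1 are loose wording, and any multiplicity rule may be in a statistical analysis plan that is not at hand.

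Much of this stands. A reader might infer that the protocol declares three co-primary tests, so that any one significant result is a primary success and the trial's error rate is 12 to 14% instead of 5%. The document does not support that. No passage states such a decision rule. The two-sided 0.05 is a sample-size input, so reproducing 91 and 122 shows how the numbers were calculated, not how claims will be made. The 12 to 14% figure also needs every null to be true, and it depends on assumed correlations. The interaction sample size is for a generic binary subgroup, with gender as the example, so it is not a power statement for H2a or H2b, where age and tear size are continuous.

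One part does not stand. Leaving the adjustment method to an analysis plan is normal, but which hypothesis is primary is something this protocol states, and it states it in two ways. An analysis plan that demoted H2a and H2b would contradict sections 2.3 and 12.2.1 as they read.

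**Conclusion.** The protocol contradicts itself on which hypotheses are primary, and the passages need reconciling. H1's own error is sound at 5%. The rate of 14.3% (about 12.5% at an assumed common correlation of 0.5) applies only if all three are treated as primary claims and all three nulls hold. The more relevant figure if surgery truly differs overall is up to about 9.8% for a false interaction claim, again if each interaction is judged at an unadjusted 0.05. The point concerns what an isolated interaction result can support; it does not weaken the test of H1.

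**What to change.** In 2.3, 12.1 and 12.2.1, name H1 as the sole primary hypothesis at two-sided 0.05. Define its contrast as the 12-month operative minus non-operative difference in SPADI change, averaged over the observed age and tear size, in line with the least-squares-means test in 12.3.3. Reword the sentence in 12.2.1 that gives all three hypotheses to the primary analysis.

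Relabel H2a and H2b as secondary, and say that neither alone supports a primary claim. Then choose one of two routes: test the pair with Holm at a two-sided family level of 0.05, or call them exploratory and report estimates with confidence intervals. If joint control of all three at 5% is wanted, also gate the pair on rejection of H1, because Holm on the pair alone does not provide it.

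The cost is wording. H1 keeps its full 0.05, with power above 99.9% for 10 points at 560 to 700 analysed (SD 19.75). Under Holm, first-step power for a generic binary 10-point interaction falls from about 92% to 87% with 700 analysed, and from about 80% to 71% at 488. The protocol gives no power for continuous age or tear size, so the loss for H2a and H2b themselves cannot be stated. The exploratory route involves no adjusted test but gives up a confirmatory claim on heterogeneity.

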**Sensitivity Analyses:** We will not rely only on Gaussian parametric modeling, as our primary mixed effects model will be cross-checked using a proportional odds regression comparing treatment effects after adjusting for baseline SPADI, study site, age, tear size, fatty infiltration, and their interactions. We will conduct full information analysis and no levels will be combined. Thus for k unique SPADI change scores, there will be k-1 levels. In addition to the primary contrast of operative versus non-operative treatment and the primary covariates, *a priori* selected independent variables include those noted in Section D.6. In model development, descriptive statistics and graphical displays of outcomes and predictor variables will be examined. Under this category we also note our plans the sequential modeling under MCAR, MAR, and MNAR missing data analyses described below. We will also perform a sensitivity analysis of the time from baseline to a 10 point (MCID) change in SPADI using Cox regression, and the binary outcome of achieving a 10-point change in SPADI, and 30% and 50% improvement in outcome scores (success) versus failure using logistic regression. We will repeat sensitivity analyses for secondary outcomes.

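### The primary SPADI model omits baseline SPADI and so gives up free precision, while the baseline-adjusted model beside it is left unranked

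*Protocol*

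**What the plan says.** Section 12.2 defines the endpoint: "the primary endpoint is the change in SPADI at 12 months relative to baseline".

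Section 12.2.1 writes out the primary mixed model for all three hypotheses. The outcome "represents the change in SPADI from baseline for participant" at 3, 6 and 12 months. The fixed effects are treatment, time, treatment by time, tear size, age, and treatment by tear size and by age. The only prognostic terms are those for which the coefficients "are the effects of tear size and age at the beginning of treatment". Baseline SPADI does not appear. The target is then named: "The estimate of interest from this longitudinal model is the predicted differential in 12-month SPADI change".

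The same section continues: "A directly parallel analysis will also be conducted". Here the outcome is the SPADI score at each visit, "with baseline SPADI as a covariate". The text illustrates the two models with two kinds of conclusion, one about improvement over 12 months and one about mean scores at 12 months. It does not call the second model secondary or supportive, and gives no rule for disagreement.

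Section 12.2.2 repeats this pair of models for ASES-SF. Section 12.4 adds, as a sensitivity analysis, a "proportional odds regression comparing treatment effects after adjusting for baseline SPADI" and other covariates.

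**The concern.** Baseline SPADI is normally among the strongest predictors of SPADI at 12 months. A change score uses it in a fixed way, by subtracting it with a coefficient of one, when the best-fitting coefficient is usually smaller. The result is a noisier treatment estimate and one that moves with chance differences in baseline SPADI. Randomisation is stratified by site, age class and tear-size class (Section 5.4.1), not by baseline SPADI, so such differences can occur. The random intercept does not recover the information, because only post-baseline changes enter the model as outcomes.

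The illustrative conclusions suggest that the two models answer different questions. Under randomisation the expected baseline difference is zero, so both estimate the same 12-month treatment difference. Two estimates of one quantity under the primary heading need a stated order. The stakes are the width of the confidence interval, sensitivity to effects below 10 points, and precision for the age and tear-size interactions in Hypotheses 2a and 2b.

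**Working it through.** **Inputs from the protocol.** SD of 12-month SPADI change 21.55 (n=45) and 19.14 (n=27), Section 12.3.1; difference of interest 10 points, Section 12.3.2; two-sided 0.05 and 350 per arm, Section 12.3.3. **Assumed, not given:** the baseline-to-12-month correlation r (0.3 to 0.7) and equal variances at the two times. The arithmetic treats the single 12-month time point.

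**1. The plan's own figure.** Pooled SD = √[(44×21.55² + 26×19.14²)/70] = 20.69. The sample size per arm for 90% power at 10 points is 90 by the normal approximation and 90.9, so 91, by the t-test. The stated 91 per arm for the unadjusted t-test reproduces.

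**2. Relative variance.** With common variance s² at both times:
- change score: 2s²(1−r)
- baseline-adjusted: s²(1−r²)
- ratio, adjusted to change: (1+r)/2

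The direction does not need equal variances. In general, with baseline SD σx and 12-month SD σy, the change-score variance minus the adjusted variance is (σx − rσy)², which is never negative.

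**3. At 350 per arm, complete data.** Change-score SE = 20.69×√(2/350) = 1.56. The adjusted SE is this times √[(1+r)/2].

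| r | Variance ratio | SE | 95% half-width (1.96×SE) | Power at 5 points |
|---|---|---|---|---|
| change score | 1 | 1.56 | 3.07 | 89% |
| 0.3 | 0.65 | 1.26 | 2.47 | 98% |
| 0.5 | 0.75 | 1.35 | 2.65 | 96% |
| 0.7 | 0.85 | 1.44 | 2.83 | 93% |

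For 10 points the change score alone has power above 99.9%. Cutting the effective sample by the stated fraction of missing information, 350×(1−0.412) = 205.8 per arm, still leaves 99.8%.

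**4. Interactions.** The contrast variance in the heterogeneity paragraph of Section 12.2.1 is proportional to the residual variance σ². Replacing σ² by σ²(1+r)/2 gives the same proportional gain for Hypotheses 2a and 2b.

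**5. Chance imbalance.** A baseline difference of d points shifts the change-score estimate relative to the adjusted one by d(1−r). For d = 2 that is 1.4, 1.0 or 0.6 points at r = 0.3, 0.5 or 0.7.

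**6. Simulation** (700 patients, 4,000 runs, no treatment effect, one time point). The two estimates correlate 0.80 to 0.92 and differ with an SD of 0.6 to 0.9 points. Each model holds about 5% type I error.

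**7. Do the models coincide once baseline is added?** Subtracting baseline from the outcome in a model that already contains baseline lowers the baseline coefficient by one and leaves everything else alone. The treatment estimates are therefore identical; in the simulation they differed by less than 1e-12.

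**The case against.** The strongest reply is that the plan is already clear and adequate. Section 12.2 defines the endpoint as change, Section 12.2.1 attaches the estimate of interest to the change-score model, and Section 12.4 refers to the primary model in the singular. The change-score estimate is unbiased under randomisation, holds its type I error, and has ample power for 10 points. A baseline-adjusted analysis is already planned for SPADI and for ASES-SF. The size of the gain depends on a correlation that the protocol does not state.

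Most of this stands. A reader might infer two competing primary estimates, but the passages above point to the change-score model as the one that decides. What is missing is a label for the second model and a rule for discordance. Claiming success if either model is significant would raise type I error to 6.5% to 7.6% in the simulation, but the protocol states no such rule. A chance imbalance shifts the estimate in a given trial; it does not bias the method.

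The reply does not show that leaving baseline SPADI out of the primary model has any advantage. A reader might also suppose that it enters through the covariate vector Zᵢ, which Section 12.2.1 says is removed for the unadjusted estimate. That vector is not in the primary equation. It is introduced in Section 12.2.2, where the examples are gender, mental health inventory and fatty infiltration.

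**Conclusion.** The point holds as one of efficiency and ranking. The primary model omits a strong, freely available covariate, and the model that includes it stands unlabelled beside it. With equal variances and r between 0.3 and 0.7, adjustment cuts the variance of the 12-month treatment difference by 35% to 15%. The conclusion on a 10-point difference is not at risk. The change is worth making but does not decide the trial's validity.

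Two further inferences are tempting and not supported:

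- **That the fall from 91 to 60 per arm in Section 12.3.3 shows the value of adjusting for baseline SPADI.** The protocol credits it only to baseline covariates, which may be tear size and age. The t-test curve uses available data and the mixed model complete cases, so model, covariates and sample all differ. The imputed adjusted model needs 82 per arm.
- **That the proportional-odds analysis is defective because it comes after "adjusting for baseline SPADI, study site, age, tear size, fatty infiltration, and their interactions".** It is offered as a cross-check on Gaussian modelling, and a sensitivity analysis may use a different covariate set.

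**What to change.** In Section 12.2.1, add baseline SPADI as a covariate to the change-score mixed model and name that model as the single primary analysis for Hypotheses 1, 2a and 2b. The endpoint stays the 12-month change. State that the model of the score with the same covariates gives the same treatment estimate, so it is another way of reporting the same result and not a second test. If the baseline coefficient is allowed to vary by visit, do so in both forms. Label the change-score model without baseline SPADI as supportive. Make the same changes for ASES-SF in Section 12.2.2.

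The cost is wording only. Section 7.3 has the baseline questionnaire completed before randomisation, so no new data are needed.
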